# Intervention for Diabetes with Education, Advancement and Support (IDEAS) study: protocol for a cluster randomised controlled trial

**DOI:** 10.1186/s12913-016-1782-y

**Published:** 2016-09-29

**Keywords:** Diabetes management, Remote monitoring, Telemonitoring, Type 2 diabetes mellitus

## Abstract

**Background:**

The high market penetration of mobile phones has triggered an opportunity to combine mobile technology with health care to overcome challenges in today’s health care setting. Although Malaysia has a high Internet and mobile penetration rate, evaluations of the efficacy of incorporating this technology in diabetes care is not common. We report the development of a telemonitoring coaching system, using the United Kingdom (UK) Medical Research Council (MRC) framework, for patients with type 2 diabetes mellitus.

**Methods:**

The Intervention for Diabetes with Education, Technological Advancement and Support (IDEAS) study is a telemonitoring programme based on an empowerment philosophy to enable participants to be responsible for their own health decision and behaviour. An iterative cycle of development, piloting, and collating qualitative and quantitative data will be used to inform and refine the intervention. To increase compliance, the intervention will be designed to encourage self-management using simple, non-technical knowledge. The primary outcomes will be HbA1c, blood pressure, total cholesterol, and quality of life and diabetes self-efficacy. In addition, an economic analysis on health service utilisation will be collected.

**Discussion:**

The mixed-method approach in this study will allow for a holistic overview of using telemonitoring in diabetes care. This design enables researchers to understand the effectiveness of telemonitoring as well as provide insights towards the receptiveness of incorporating information technology amongst type 2 diabetes patients in a community setting.

**Trial registration:**

ClinicalTrials.gov NCT02466880 Registered 2 June 2015.

## Background

Globally, an estimated 385 million people are living with diabetes, and this is expected to increase to 552 million by 2030 [1, 2] . This increasing prevalence of diabetes, especially type 2, poses a major public health concern, as it is associated with substantial morbidity, mortality, as well as financial cost due to the associated microvascular and macrovascular complications. In Malaysia, type 2 diabetes affects approximately 12 % of the total population and, together with ischaemic heart disease, constitute nearly 75 % of the total non-communicable disease burden [3]. Clinical care of diabetes currently consumes approximately 16 % of the total national healthcare budget in Malaysia, with an estimated RM2.4 billion (about USD0.55 billion) spent in 2010 [4]. A recent study in Malaysia reported that patients with diabetes spent up to 14.7 % of their household income on outpatient diabetes care [5].

The utilization of self-monitoring blood glucose (SMBG) for individuals with diabetes is low, with only 6.9 and 26.8 % of people with diabetes utilising SMBG in private and public hospitals, respectively [6]. The utilisation of SMBG in people with diabetes is complex. Financial, psychological, and behavioural factors can affect an individual’s utilisation of SMBG [6–8]. Innovative methods are required to overcome these challenges. Currently, with the advancement of technology, there is a promising potential to overcome such barriers [9, 10].

Remote patient monitoring or telemonitoring has recently gained much attention as a promising and innovative solution to improve patient care and management from a distance, especially for those with diabetes. It involves the use of telecommunication technologies such as video, audio, handheld technologies or intelligent sensors for the digital transmission of physiological and other disease related data for monitoring patient’s condition and clinician’s feedback [11, 12]. Systematic reviews of telemonitoring intervention in diabetes, asthma, heart failure and hypertension showed that telemonitoring is a safe, effective and acceptable intervention method with better glycaemic control, significant improvements in peak respiratory flows and reduction in systolic or diastolic blood pressure [13, 14]. Additionally, due to the algorithmic structure of computerised systems, data reported by patients were entirely accurate, overcoming the challenges of inaccurate results [15–17].

However, there is limited evidence regarding the feasibility of translating telemonitoring research into practice in a developing country such as Malaysia. Malaysia with a population of 29 million people has a mobile penetration rate of 140 %, indicating that 47 % of Malaysians own more than one mobile phone [18, 19]. Furthermore, Malaysia has a total of 20 million Internet users and 15 million people are subscribers of third generation (3G) networks, indicating a potential to incorporate mobile telemonitoring among the general public [18, 19]. Therefore, this study will design a system, which incorporates current technology, and evaluate the practicality of such a system in patient care, for people diagnosed with type 2 diabetes in Malaysia. The focus of the study will be on the use of remote monitoring to maximise the use of information and communications technology (ICT) to deliver lifestyle intervention, provide accurate data, as well as influence patients’ attitude and behaviour in a community setting in Malaysia. This study will include various factors working interdependently with each other, including an automated feedback mechanism for diabetes monitoring, cost effectiveness, diabetes education as well as a focus group to understand participants point of view for future intervention implementation. The UK Medical Research Council (MRC) framework for complex intervention will be used to guide the development and evaluation of this current study.

This framework emphasises that the development, evaluation and implementation of any complex intervention require a strong theoretical foundation [20, 21]. Furthermore, a wide spectrum of intervention studies which required behavioural changes, information services, education programmes, integrated systems of patient care and complementary therapies have been conducted using this approach [21, 22]. The MRC framework suggests a progression of different phases, starting from the pre-clinical phase up to phase IV clinical trials (Fig. 1). This article will discuss how the MRC framework criteria are used to develop the current study.

**Fig. 1 Fig1:**
[figure not shown]
MRC framework adapted from Higginson et al. *BMC Palliative Care* 2006 5:7 [22]

## Methods/design

### Aim of the study

The aim of this cluster randomised controlled study is to evaluate the effectiveness of the Intervention for Diabetes with Education, Technological Advancement and Support (IDEAS) among type 2 diabetes adults, in reducing serum HbA1c levels. The IDEAS involves data transmission, feedback and education.

### Outcome measures

The primary outcome of this study is changes in HbA1c levels pre and post intervention. Secondary outcome measures include changes in body weight, fasting blood glucose, blood pressure, quality of life and physical activity.

### Theoretical framework

The Health Belief Model (HBM) forms the basis for the theoretical underpinning of this study [23]. HBM is a conceptual framework that has been used extensively to explain health behaviour [24]. However, the theoretical HBM does not suggest a strategy for changing health-related actions. Therefore, modifying factors which include media, health professionals, personal relationships, incentives and self-efficacy of recommended health action create a “cue to action” for patients to elicit behaviour compliance.

### Articulation of study to HBM framework

Perceived barriers to self-care can hinder progress in patient participation. Several perceived barriers deter patient participation in regular SMBG. These include inconvenient programme days and time, lack of feedback, lack of reminders and the cost [25]. This study is designed to address these common barriers. To make participation convenient, follow-up sessions will be scheduled during participants’ regular appointments at the clinics. To address the barrier of time, diabetes classes will last for a maximum of one hour, screening and follow-up consultations will take approximately 1 h, while focus group sessions will last up to 2 h, will be conducted at separate sessions. Therefore, total contact time commitment for the entire programme will be seven and a half hours over a span of 1 year. To overcome the lack of feedback, participants in the telemonitoring group will receive an automated e-mail reminder if self-monitoring of blood glucose is not performed for three consecutive times while monthly follow-up calls to participants in the control group will be conducted. Furthermore, feedback will be provided to participants if blood glucose results show three continuous blood glucose values of ≤ 3.9 mmol/l or ≥11.1 mmol/l in the telemonitoring group. To overcome the cost barrier, the programme will be offered free to all participants.

### Multidisciplinary committee

In order to enhance the community-specific intervention of the study, a multidisciplinary committee will be established to receive input from various experts including doctors, pharmacists and nurses. The committee will also provide assistance in participant enrolment, patient counselling and disease education.

### Phase 0–1: theoretical phase/modelling

The theoretical basis of this study was established by reviewing published literature on the utilisation of mobile technology in diabetes care [26–31]. To develop a cultural-specific telemonitoring system that is suitable for the Malaysian population, evidence of poor diabetes management and its additional associated risks during Ramadan was reviewed [32, 33]. This allowed for specification of the required interventions that would accommodate an ethnically diverse country like Malaysia.

### Phase 2: exploratory trial

This exploratory phase of the study focused on the use of telemonitoring during the holy month of Ramadan. During this period, Muslims are required to refrain from consuming food and water from dawn till dusk. Studies have shown that modified dietary habits could increase the risk of severe hypoglycaemia by nearly 7.5-fold [33, 34]. Therefore, the objective of this exploratory phase was to evaluate the effects of implementing a telemonitoring programme to aid Muslims with type 2 diabetes who were fasting during Ramadan. Ethics approval for this study has been obtained from the Medical Research and Ethics committee, Malaysia (NMRR-14-177-19466) and Monash University Research Ethics Committee (CF14/1977-2014001016).

Eligible participants included those who had been diagnosed with type 2 diabetes, aged 18–75 years, with HbA_1c_ level between 7.5 and 11 %, willing to fast for 15 days, had internet access, an e-mail address and a smartphone, and provided informed written consent. Patients from five public health care centres were allocated into usual care group (*n* = 19) *or* telemonitoring group (*n* = 18) using clustered randomisation method. Education materials which focused on diabetes management during Ramadan were provided to participants to standardise education level as well as diabetes management practice.

During the 7-week intervention, a web-enabled glucose meter (Entra Health System, San Diego, CA, USA), connected to an android phone, which could transmit recorded blood glucose results to a web portal, was provided to all participants in the telemonitoring group. The device also provided automatic feedback to the participant if his/her recorded blood glucose results for three continuous tests were ≤ 3.9 mmol/l or ≥11.1 mmol/l. A schematic diagram representing the elements of this system is shown in Fig. 2. Diaries were provided to all participants in the study to record any hypoglycaemic events that occurred during the study. Participants were encouraged to self-monitor their blood glucose levels five times a day during the month of Ramadan. Ten focus group sessions were conducted to elicit participants’ experiences of fasting during the month of Ramadan as well as the study design.

**Fig. 2 Fig2:**
[figure not shown]
Technical schema of the proposed telemonitoring system

Results from the pilot study showed that hypoglycaemic episodes were lower in the telemonitoring group compared to the usual care group [35]. Focus group discussion indicated that participants were open to new technologies, which helped them in managing their disease. Several limitations were noted during the exploratory phase of the study. These were mostly related to the study design. Since participants had to be recruited when they were fasting during the month of Ramadan, this limited the recruitment time and hence, the small sample size. In addition, difficulty in accessing Internet connection affected the delivery of the blood glucose results to the researchers.

### Randomised controlled trial (phase III)

The exploratory phase was conducted in a specific population within a seasonal time period and generalisability of the results could be limited. Generalisation to a larger and more diverse population remains to be tested. To overcome these limitations, we describe the design of a larger study (IDEAS Study), which will take into considerations the limitations noted in the pilot study.

### Randomisation

The study will follow a cluster randomised design with the public clinics as the unit of randomisation. This will avoid potential contamination between individuals who are assigned to different treatment groups in the same study site. A trained individual, independent of the study team will conduct all the randomisation.

### Sample size calculation

A previous study in a tertiary hospital reported a 0.79 % mean difference in HbA1c between adherent and non-adherent people with diabetes [36]. A sample size of 100 people per study arm will have an 80 % power to detect a 0.5 % difference in HbA1c between the intervention and control arm. Therefore, after accounting for a 20 % loss to follow-up in each arm, 240 people with diabetes will be recruited in this study.

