#### Quantitative data analysis

Analysis of quantitative study data across randomised groups will be conducted in IBM SPSS version 20 (Armonk, NY). Continuous variables will be tested for normality and data, which are not normally distributed, will be analysed using Kruskal-Wallis and Wilcoxon signed ranks test. In the event of missing data, the last observation carry forward method will be used. A *p* value of < 0.05 will be considered as statistically significant for all the tests.

Effectiveness of the research intervention will be measured in terms of differences between study arms with respect to changes in biomedical measures and activities. Logistic regression will be used and both adjusted and unadjusted models will be presented. Benefits, barriers, confidence and knowledge will be included in a model to identify factors associated with the concept of intensive treatment and hypoglycaemia. An adjusted *t*-test using multiple linear regression analysis will be conducted to calculate variables for benefits, barriers and knowledge.

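### The 80% power is tied to people per arm alone, so it is not shown to hold for a trial that randomises clinics

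*Protocol article*

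**What the plan says.** The Randomisation section of the protocol article fixes the design: "The study will follow a cluster randomised design with the public clinics as the unit of randomisation".

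The Sample size calculation section follows it directly. It cites a 0.79% "mean difference in HbA1c between adherent and non-adherent people with diabetes" from an earlier study, without an SD. Its power claim begins with the words "A sample size of 100 people per study arm will have an"; the figure given is 80%, and the target is a 0.5% "difference in HbA1c between the intervention and control arm". From there it allows for 20% loss to follow-up in each arm and arrives at 240 people.

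The article gives no SD, ICC, design effect, number of clinics or clinic size for the main trial. The significance level appears only under Quantitative data analysis: a p value below "0.05 will be considered as statistically significant for all the tests". That section names Kruskal-Wallis and Wilcoxon signed ranks tests, logistic regression and multiple linear regression, and mentions no term for clinic.

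**The concern.** Patients at one clinic share doctors, local practice and case mix, so their HbA1c values tend to be correlated. When whole clinics are randomised, that correlation inflates the variance of the difference between arms. The number of clinics, and not only the number of patients, limits the information available. A power figure that depends only on people per arm leaves both effects out of sight.

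HbA1c is the primary outcome, and the article says its results are meant for policy makers. If true power for a 0.5 difference is well below 80%, a null result could be read as evidence against an effect that the trial had only a moderate chance of detecting.

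**Working it through.** **Inputs from the article.** 100 evaluable people per arm, a difference of 0.5, power 80% (Sample size calculation); alpha 0.05 (Quantitative data analysis); clinics as the unit of randomisation (Randomisation).

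**Assumed, because not given.** Two-sided testing; SD 1.0, 1.26 or 1.5; 5 or 10 clinics per arm of equal size; ICC 0.01, 0.03 or 0.05.

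**Step 1: the plan's own figure.** It cannot be reproduced without an SD, so the SD has to be solved for. In a plain two-sample t-test with 100 per arm, two-sided alpha 0.05 and 80% power, the standardised difference is 0.398, so SD = 0.5/0.398 = 1.256. The normal approximation gives 0.5/[(1.960 + 0.842) × √(2/100)] = 1.262. One-sided testing would give 1.42. This shows which SD matches an individual-level calculation. It does not show that such a calculation was done.

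**Step 2: room for clustering under other SDs.** Individual-level n per arm = 2 × (1.960 + 0.842)² × SD²/0.5².
- SD 1.0: 63 per arm, so 100 leaves room for a design effect of 100/63 = 1.59.
- SD 1.5: 142 per arm; 100 per arm gives 65% power even with no clustering.

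**Step 3: apply clustering.** With k clinics per arm, m = 100/k. Design effect DE = 1 + (m − 1) × ICC; effective n = 100/DE; SE = SD × √(2/effective n). Power comes from a noncentral t with 2(k − 1) degrees of freedom and noncentrality 0.5/SE.

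Example, k = 5, ICC 0.03, SD 1.256: m = 20; DE = 1 + 19 × 0.03 = 1.57; effective n = 63.7; SE = 0.223; noncentrality = 2.25. Against a critical value of 2.306 on 8 df, power is 51%.

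The design effects are 1.19/1.57/1.95 for 5 clinics per arm and 1.09/1.27/1.45 for 10.

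| SD | Clinics per arm | Power at ICC 0.01 / 0.03 / 0.05 | Difference detectable at 80% power |
|---|---|---|---|
| 1.0 | 5 | 81 / 70 / 60% | 0.49 / 0.57 / 0.63 |
| 1.0 | 10 | 89 / 84 / 79% | 0.44 / 0.47 / 0.50 |
| 1.26 | 5 | 62 / 51 / 43% | 0.62 / 0.71 / 0.79 |
| 1.26 | 10 | 72 / 66 / 60% | 0.55 / 0.59 / 0.63 |
| 1.5 | 5 | 48 / 38 / 32% | 0.74 / 0.85 / 0.95 |
| 1.5 | 10 | 57 / 51 / 46% | 0.66 / 0.71 / 0.76 |

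The detectable difference is 3.20 × SE on 8 df and 2.96 × SE on 18 df, against 2.80 × SE under the normal approximation.

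**Step 4: separate the two effects.** With the normal approximation, so that only the design effect acts, power at SD 1.256 is 73/61/52% with 5 clinics per arm and 77/70/65% with 10. With ICC = 0, so that only the loss of degrees of freedom acts, it is 69% with 5 clinics per arm and 76% with 10.

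**The case against.** The strongest reply is that the article does not say the 100 were treated as independent. It omits the SD, which any calculation must have used, so the absence of an ICC does not prove that none was used. Solving for SD 1.26 presupposes no clustering allowance and so cannot be evidence that there was none. A smaller SD is not far-fetched. Entry HbA1c is limited to 7.5% up to 11.0%, and a uniform spread over that range has SD 3.5/√12 = 1.01. The primary outcome is change in HbA1c, whose SD is also not given. At SD 1.0 with 10 clinics per arm, power on clinic-level degrees of freedom is 89/84/79%, which meets the 80% or misses it by one point. A journal article may also leave these inputs to a full protocol that is not shown.

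Much of this stands. A reader might infer that the sponsor demonstrably ignored clustering, or that the design simply lacks 80% power. The article supports neither as fact. Nor is this a demonstrated miscalculation, since the 80% can be neither reproduced nor refuted.

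What does not stand is the step from condensed reporting to no problem. Missing inputs can be excused. A stated power for a clinic-randomised trial, expressed only in people per arm and carried to the recruitment target with attrition as the sole adjustment, is a claim made in the text. The favourable scenarios also need a small SD together with a low ICC, more clinics or both, and the article states none of these. With SD 1.0 and 5 clinics per arm, power falls to 70% at ICC 0.03.

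**Conclusion.** The 80% is an unsupported power statement for this design. The likeliest reading is an individual-level calculation: attrition is the only adjustment named, and the analysis section mentions no clinic term. On that reading the power is overstated: about 62% to 43% with 5 clinics per arm, or 72% to 60% with 10, for ICC 0.01 to 0.05. If the SD is nearer 1.0, the stated power may be met or nearly met with 10 clinics per arm; if it is nearer 1.5, power is below 60% in every scenario examined.

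These sizes depend on the assumed SD, ICC, number of clinics, equal clinic sizes and two-sided testing, and on 100 people analysed per arm. Confidence is medium: firm that the claim is not shown for the design, less firm on how far the true power differs from 80%.

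**What to change.** Keep recruitment as it is. In the Sample size calculation section, state the SD (and whether it is for HbA1c at follow-up or for change), the number of clinics per arm and an ICC range with its source. Apply the design effect 1 + (m − 1) × ICC and clinic-level degrees of freedom. Replace the present power claim with the resulting power for a 0.5 difference, or with the difference detectable at 80% power. If clustering was already counted in the 100, show the inputs that do so, and the claim can stay. Use the same figure when interpreting a null result.

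The cost is wording and a short recalculation, with no extra patients. The downside is that the stated power will probably look less favourable.

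### The 20% loss allowance multiplies by 1.2 instead of dividing by 0.8, so 240 recruits leave 96 per arm with complete follow-up, not 100

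*Protocol article*

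**What the plan says.** The whole calculation stands in the protocol article, Methods/design, under Sample size calculation. It gives three linked figures:

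- The number needed: "A sample size of 100 people per study arm will have an 80 % power", for a "0.5 % difference in HbA1c between the intervention and control arm".
- The allowance: the total is reached "after accounting for a 20 % loss to follow-up in each arm".
- The result, in the same sentence: "loss to follow-up in each arm, 240 people with diabetes will be recruited in this study".

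The result is presented as following from the first two, so 240 is meant to preserve 100 per arm once losses have occurred. No other section gives a different recruitment total, per-arm number or definition of loss. The section states no standard deviation, significance level or design effect. The 0.05 level comes from Quantitative data analysis, which does not say whether tests are one- or two-sided.

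**The concern.** The paragraph prints both its inputs and its result, and they do not agree. Taking 20% away from 240 does not give back the 200 from which the calculation started. Condensing a full protocol into an article would not explain this, because nothing has been left out of the step in question.

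At stake are the trial's recruitment target and the claim attached to it, namely that the trial can lose a fifth of each arm and still have the number on which its power statement rests. The allowance has real work to do here, since Table 1 schedules measurements up to visit 52.

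**Working it through.** **Inputs, all from Sample size calculation unless noted**

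- Needed per arm after losses: 100
- Loss: 20% in each arm
- Recruited: 240 in total, which is 120 per arm if arms are equal (implied by the single per-arm figure, not stated separately)
- Difference: 0.5 percentage points of HbA1c; power 80%
- Significance level 0.05 (Quantitative data analysis), two-sided assumed; needed only for step 4

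**1. Reproducing the plan's figure**

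n × (1 + loss) = 100 × 1.20 = 120 per arm; 2 × 120 = 240. This matches exactly.

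**2. The inflation that preserves 100 per arm**

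n / (1 − loss) = 100 / 0.80 = 125 per arm; 2 × 125 = 250. The stated total is 10 recruits short (10/240 = 4.2%), too much for rounding.

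**3. What 240 delivers**

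- At 20% loss: 120 × 0.80 = 96 per arm, 192 in total.
- Largest loss that still leaves 100 per arm: 1 − 100/120 = 16.7%.

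Steps 1 to 3 do not depend on the standard deviation, the significance level or clustering.

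**4. Consequence for power (conditional)**

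Because no standard deviation is given, one is back-solved on the assumption that 100 per arm gives exactly 80% power, with individuals treated as independent:

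- SD = 0.5 / [(1.960 + 0.842) × √(2/100)] = 1.26
- Power at 96 per arm = Φ(0.5 / [1.262 × √(2/96)] − 1.960) = Φ(2.745 − 1.960) = 78.4%

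A t-test calculation gives an implied SD of 1.256 and the same 78.4%. With a one-sided 0.05 level the implied SD is 1.42 and power at 96 is 78.6%.

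The range over other standard deviations (two-sample t-test, two-sided 0.05, difference 0.5, no clustering):

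| SD | Power at 100 per arm | Power at 96 per arm |
|---|---|---|
| 1.20 | 83.4% | 81.9% |
| 1.23 | 81.6% | 80.0% |
| 1.25 | 80.4% | 78.7% |
| 1.256 | 80.0% | 78.4% |

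The drop of about 1.6 points is nearly constant across the table. Whether power ends up above or below 80% depends on the SD.

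**The case against.** Three points can be made in the plan's defence.

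*Power may not be missed.* A reader might infer from the shortfall that the trial falls below 80% power on its own assumptions. The document does not establish this. The figure of 100 is round, and 80% may be a rounded or minimum value. If the planners had in mind an SD of 1.23 or lower, 96 per arm still reaches 80%. This objection stands: only the recruitment shortfall follows from the document alone.

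*Participants who are lost may still be analysed.* Quantitative data analysis plans to carry the last observation forward, and Table 1 includes a visit 0, so anyone with a baseline value has something to carry. A reader might infer that 96 per arm will be analysed; under that rule the analysed number could be nearer 120. This also stands, and it is why 96 is described here as the number with complete follow-up. It does not rescue the arithmetic. If carried-forward values counted towards the 100, no allowance for loss would be needed at all, and carrying values forward does not restore the lost information.

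*The effect is small and the timing late.* Both are true. The Discussion dates the start of recruitment to April 2015 and the end of data collection to December 2016. If visit 52 means week 52, raising the target to 250 was probably no longer practical when the article appeared in September 2016. That bears on the choice of correction, not on whether the sentence is right.

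**Conclusion.** The point holds as a minor correction to a stated figure. The allowance was applied with the wrong formula, and 240 recruits do not leave 100 per arm at the 20% loss named in the same sentence. The gap is 4 people per arm with complete follow-up, or 10 recruits overall. The only assumption behind this is equal arms.

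The cost in power is about 1.6 points before any design effect. The fall from 80% to about 78.4% is conditional on 100 per arm giving exactly 80%, a two-sided 0.05 level and no clustering. It should not be reported as a demonstrated loss of the 80% target. No endpoint, design feature or analysis method changes as a result.

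**What to change.** Restate the last sentence of Sample size calculation so that the loss statement is true. For example: 240 people will be recruited; this retains 100 per arm with complete follow-up at up to 16.7% loss, and at 20% loss 96 per arm remain. This costs one sentence and no additional participants.

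If the authors prefer to keep both the 20% loss and the 100 per arm as claims, the total has to read 250, which means 10 more recruits.

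The stated 80% should not simply be replaced by 78%. That number rests on a back-solved standard deviation that the protocol never gives, and it treats participants as independent although clinics are randomised. If a power figure for 96 per arm is wanted, it should be given together with the SD assumed and labelled as before any design effect.
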